### Analysis

All statistical analyses will be performed using SAS (version 9.3) statistical software. Using intention to treat principles, differences between groups in both costs and outcomes will be assessed using hierarchical linear (or logistic for binary outcomes) regression models, adjusting for pre-specified prognostic variables and random effects for repeated measures on students. Missing data will be imputed using multiple imputation methods. All statistical tests will be two tailed with an alpha of 0.05. Students intending to purchase their lunch from the canteen will be removed from the primary analysis to focus on students whose lunchbox is their sole source of energy for the day [23].

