### Randomisation and blinding

Following baseline data collection, schools will be randomly allocated to intervention or control via block randomisation on a 1:1 ratio using a computerised random number function. Randomisation will be stratified by the socioeconomic status of school locality using the Socio-Economic Index for Area (SEIFA 2006), as socioeconomic status is associated with child dietary intake [30, 31]. Randomisation will be undertaken by a statistician not involved in contacting schools in the study intervention or assessment. Data collectors and lunchbox analysis dietitians will be blinded, but school principals will be notified of their group allocation.

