
### Sample size and power calculations

Based on our pilot results, a standard lunchbox contains 1089 kJ (SD = 900 kJ) from discretionary foods. With an ICC of 0.05, 36 schools with 140 students per school will enable detection of a 200 kJ difference between groups at follow-up on the primary trial outcome, with 80% power at the 0.05 significance level. As approximately 420 kJ across a whole day has potential to reduce the prevalence of childhood obesity [18, 19], and a child consumes a third of their daily energy requirements whilst at school [11], this magnitude of effect is considered meaningful at a population level.

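### The primary model does not say which term is the treatment effect; a baseline-adjusted 5-month difference would match the powered contrast and is more precise than a change contrast

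*Protocol article*

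**What the plan says.** - **Model (Analysis).** By intention to treat, "differences between groups in both costs and outcomes will be assessed using hierarchical linear (or logistic for binary outcomes) regression models". The sentence goes on to promise adjustment for prognostic variables fixed in advance, which it does not list, and random effects for the repeated measurements on students. Missing data are to be multiply imputed.
- **Measurement times (Design; Primary outcome).** Discretionary energy packed is measured at baseline and at 5 months, and at no other time. Schools are randomised after baseline collection, so the baseline value is a genuine pre-randomisation covariate.
- **Powered contrast (Sample size and power calculations).** Taking 140 students in each of 36 schools and an ICC of 0.05, the article claims that this size "will enable detection of a 200 kJ difference between groups at follow-up on the primary trial outcome". The claimed power is 80% at the 5% level, and no credit is taken for baseline.
- **Stratum (Randomisation and blinding).** Allocation is stratified by the SEIFA score of the school's locality, on the ground that socioeconomic status is related to children's diet. The Analysis section does not mention SEIFA.

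**The concern.** With two time points, repeated measures on students means that baseline is modelled as an outcome. Such a model can give more than one estimate of effect. With baseline means left free in each arm, the usual effect is the group-by-time interaction, which is a difference in change. With a common baseline mean, it is the baseline-adjusted difference at 5 months. The article does not choose between them, and only the second keeps the powered contrast while using baseline to sharpen it.

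A change contrast carries the full noise of the baseline measurement, which here is one lunchbox on one day. The trial has 36 schools and its power calculation leaves no margin. The cost-effectiveness analysis is also conditional on efficacy. Leaving the term open further allows the contrast to be chosen after the data are seen.

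The stratum raises a smaller point of the same kind. The design balances on SEIFA because it is thought prognostic, and that balance yields precision only if the model includes it.

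**Working it through.** **Inputs from the article:** SD 900 kJ ("a standard lunchbox contains 1089 kJ (SD = 900 kJ) from discretionary foods"), ICC 0.05, 18 schools per arm, 140 students per school, difference 200 kJ. On sidedness: "All statistical tests will be two tailed with an alpha of 0.05".

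**1. The plan's own figure.**
- Design effect = 1 + 139 × 0.05 = 7.95.
- Effective n per arm = 18 × 140 / 7.95 = 317.0.
- SE of the follow-up difference = 900 × √(2 / 317.0) = 71.5 kJ.
- Power = Φ(200 / 71.5 − 1.96) = 79.9%. The stated 80% reproduces. With a t reference on 34 df it is 77.6%.

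**2. Variance of each contrast relative to the follow-up difference.** Let r be the correlation of a school's mean between the two times, with equal variance at both times and the same students measured twice.
- Unconstrained group-by-time (change) contrast: 2(1 − r).
- Baseline-adjusted difference: 1 − r².
- The first minus the second is (1 − r)², which is positive for every r below 1. The ranking therefore needs no assumed correlation.
- The change contrast is worse than ignoring baseline when 2(1 − r) > 1, that is, when r < 0.5.
- A generalised least squares check on school means gives a repeated-measures model with a common baseline mean variance factors of 0.91, 0.75 and 0.51 at r = 0.3, 0.5 and 0.7. These equal 1 − r² exactly. The unconstrained contrast gives 1.4, 1.0 and 0.6.

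**3. Illustrative sizes.** The article gives no correlation over time, so these are assumptions. With school-level correlation c and student-level correlation s, r = (140 × 0.05 × c + 0.95 × s) / 7.95. Take s = 0.3. For c = 0.5, r = (3.5 + 0.285) / 7.95 = 0.476. The change SE is 71.5 × √1.048 = 73.2 kJ and the adjusted SE is 71.5 × √0.773 = 62.9 kJ.

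| c | r | Change: variance factor | Change: power | Adjusted: variance factor | Adjusted: power |
|---|---|---|---|---|---|
| 0.2 | 0.21 | 1.58 | 61% | 0.96 | 82% |
| 0.4 | 0.39 | 1.22 | 71% | 0.85 | 86% |
| 0.5 | 0.48 | 1.05 | 78% | 0.77 | 89% |
| 0.8 | 0.74 | 0.52 | 97% | 0.45 | 99% |

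Power is for 200 kJ by the normal formula. Follow-up only is 79.9% throughout. Taking s = 0.4 instead moves these figures by about one point (at c = 0.5, 79% and 89%).

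**4. Stratum.** Suppose SEIFA removes a share R of the between-school variance. The variance factor is then (0.95 + 7 × (1 − R)) / 7.95. For R = 0, 10, 20 and 30%, power on a t reference with 33 df is 77.5, 81.1, 84.9 and 88.6%. If SEIFA explains nothing, the cost is 77.6% to 77.5%. R is also an assumption.

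**The case against.** The strongest reply is that the article nowhere states a change contrast. It mentions no interaction, change score or free baseline means, and the sample size section does name a difference at follow-up. A repeated-measures model with a common baseline mean fits both sections and is as precise as covariate adjustment. This stands. A reader might infer that the plan commits to a change analysis, or that treating baseline as an outcome is itself inefficient, but the text supports neither. The loss belongs to one reading that the text leaves open.

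A reader might also infer that SEIFA is left out of the model. The article shows only that SEIFA is not named. The reason given for stratifying makes it a natural member of the prognostic set, and baseline could be in that set too. A condensed article may leave the list to the full protocol or analysis plan, so the missing list is not a fault.

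The size of any gain also depends on unknown correlations. At a school correlation of 0.8 even the change contrast does much better than the powered analysis, and the gap to the adjusted one is 97% against 99%.

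What remains does not depend on these points. The article commits to a model form without tying it to the contrast it powers, and the adjusted estimate is the more precise choice at any correlation below 1, apart from a small loss of degrees of freedom.

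**Conclusion.** The point holds as a recommendation on precision and clarity. The planned analysis is not invalid, and the sample size has no arithmetic error.

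- **Certain:** the article does not say which term of the repeated-measures model is the treatment effect. An unconstrained change contrast would have 2(1 − r) times the variance of the powered contrast, and baseline adjustment always does better.
- **Conditional:** power below the stated 80% requires both the unconstrained reading and r < 0.5. At the illustrative r of about 0.48, the SE is 14% smaller with adjustment (62.9 against 73.2 kJ) and power is about 89% against 78%. At r of about 0.74 the SE is 7% smaller and power hardly differs.
- **Not shown:** that SEIFA is omitted from the model, or that precision will in fact be lost.

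**What to change.** State in the Analysis section, or in the analysis plan before unblinding, wording such as: *The primary estimate is the between-group difference at 5 months from a mixed model adjusted for the student's baseline value, the school's mean baseline value and SEIFA stratum, with a random effect for school.* The equivalent repeated-measures model with a common baseline mean in the two arms, also including SEIFA stratum, serves as well, provided the 5-month group difference is named as the estimate. Use the same model for the dietary secondary outcomes measured at both times.

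The cost is wording only, because baseline values and the stratum are already collected. The downside is one or two between-school degrees of freedom out of about 34. In the covariate version, students without baseline data also rely on the planned multiple imputation.

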### Trial discontinuation or modification

It is not anticipated that any events would occur that would warrant discontinuing the trial. Any unforeseen adverse events will be reported to the Hunter New England Human Research Ethics Committee (primary approval committee) and advice sought regarding required action. The trial registration record will be updated with any protocol modifications and any deviations from original protocol will be reported in study outcome papers.

## Discussion

There is currently scarce evidence available regarding the effectiveness and cost effectiveness of interventions to support parents and primary schools in improving the nutritional quality of the foods packed in school lunchboxes. Internationally, there have been few RCTs with only five interventions published that have aimed to improve the nutritional quality of school lunchboxes and those conducted have largely failed to reach parents, were resource intensive and logistically challenging to deliver at scale [20]. The SWAP IT trial will be the first m-health based trial to assess the effectiveness of a lunchbox intervention targeting primary schools, children and their parents. A pilot of the intervention [23] indicated it to be highly feasible, acceptable to both parents and schools, and showed promising signs in reducing mean energy content of packed foods at a population level.

With scalability at the forefront of the intervention design, SWAP IT has been designed in collaboration with all key stakeholders and in partnership with key industry organisations in order to meet a policy objective to impact on childhood overweight and obesity at a population level. Using technology as the primary mode of delivery into the home environment, the intervention has been designed to overcome the barriers identified in the literature in improving the nutritional quality of lunchboxes and provides a means for reaching large number of parents. However, as the intervention is embedded within existing school communication systems and processes with which both schools and parents are actively engaged, findings of the pilot found that exposure to the intervention continues across the delivery period. Embedding behaviour change interventions within existing technological infrastructure provides a unique platform to scale-up the SWAP IT intervention, if shown to be effective.

## Data Availability

The datasets analysed during the study can be made available from the corresponding author on reasonable request, once the study is completed. All data will be stored securely as per ethical requirements. All participants will be issued a unique identification number following consent for confidentiality. The final trial dataset will be stored securely and accessed only by the study statistician. The results of this trial will be disseminated via publication in peer reviewed journal, conference presentations and reports to schools and relevant health and education departments.

## Abbreviations

ACAES: Australian Child and Adolescent Eating Survey
BCW: Behaviour Change Wheel
CC: Central Coast
HNE: Hunter New England
kJ: Kilojoules
LHD: Local Health District
MNC: Mid North Coast
NSW: New South Wales
RCT: Randomised Controlled Trial
SEIFA: Socio-Economic Index for Area
SFC: School Food Checklist
